### Analysis

We will use repeated measures analysis for all recorded measurements of HbA1c, blood pressure, cholesterol and fasting blood glucose to optimally use all available data. Data from the questionnaires at the start and at the end of the intervention period will be analysed using ANCOVA. Data will be analysed according to intention-to-treat. For handling missing data we will use multiple imputation [18]. After the intervention, the randomised three-monthly and six-monthly monitoring groups are compared on equivalence of cardiometabolic control.

Since this trial is a patient preference trial, we will also compare the three-monthly preference group with the three-monthly randomised group. Depending on the number of patients opting for the six-monthly controls, we will compare this group with the six-monthly randomised group. In these analyses, we will examine determinants of preference, and we will determine risk profiles of patients. This will facilitate the applicability of the results and we can demonstrate if people who are more motivated will have better cardiometabolic control. Figure 2 provides an overview of all comparisons that will be made between the groups.

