**Figure 1 F1:**
[figure not shown]
**Participant flowchart**. The participant flowchart with the expected number of patients, based on a small survey.

We chose to conduct a patient-preference trial because of two reasons [7]. First, it gives us the possibility to compare the relationship between patients' preference for a frequency of diabetes control and the study outcomes. Second, more people will participate in the study, as people can choose not to be randomised; they can be included in the so-called 'observational' study arm of their choice. Doing so, we will have information about people who are not randomised and this will help in generalising the results. In conducting a patient-preference trial we will avoid selection and probably also drop-out after randomisation.

We chose to conduct an equivalence trial, because we want to assess whether six-monthly monitoring results in equal cardiometabolic control compared to the current frequency of control [8]. Since we expect that six-monthly monitoring will not give better cardiometabolic control than three-monthly monitoring, we did not choose a non-inferiority trial. The intervention period will last one and a half year, so patients will be seen either seven or four times during the intervention period.

The Medical Research Ethics Committee of the University Medical Center Utrecht has approved the study protocol (Protocol number: 08-453).

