### Recruitment of practices and patients

We will approach the boards of several health care groups to recruit general practitioners. These health care groups have a central database in which all type 2 diabetes patients are recorded. In this database all determinants that are needed for the selection of study patients are included (see **study population **for the inclusion criteria). The health care groups will ask all their affiliated general practitioners to participate in the study. If a general practitioner wants to participate he will obtain the selection of patients, according to the inclusion criteria, from the health care group. The general practitioner sends an information letter as well as an informed consent form to the selected patients.

Patients who want to participate have to fill in the informed consent form. The participants are asked whether they strongly prefer three-monthly (current care) or six-monthly diabetes control or whether they have no preference. Patients with a preference will enter the 'observational arm'. If participants do not have a strong preference for the frequency of care, they will be randomised.

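### Comparing self-selected preference groups with randomised groups cannot show whether more motivated patients have better control, because motivation is not measured and a preference for a visit frequency is not motivation

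*Protocol article*

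**What the plan says.** Under Recruitment of practices and patients, consenting patients state whether they strongly prefer three-monthly or six-monthly control. Those with a strong preference are not randomised. The Study design section says of people who do not wish to be randomised that "they can be included in the so-called 'observational' study arm of their choice". Only patients without a strong preference are allocated at random.

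The Analysis section adds two comparisons to the main one. First, "we will also compare the three-monthly preference group with the three-monthly randomised group". Second, "Depending on the number of patients opting for the six-monthly controls, we will compare this group with the six-monthly randomised group". Within these analyses "we will examine determinants of preference, and we will determine risk profiles of patients". The section then states what the comparisons are expected to yield: "we can demonstrate if people who are more motivated will have better cardiometabolic control".

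The Study design section gives a more cautious purpose for the preference design: "it gives us the possibility to compare the relationship between patients' preference for a frequency of diabetes control and the study outcomes".

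**The concern.** Within each pair the visit frequency is the same, so the groups differ in who chose to be there. A difference in cardiometabolic control could then have at least three sources: a different risk before the study, an effect of receiving the frequency one asked for, or a difference in motivation. The comparison does not separate them, and the third is not observed at all.

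The plan nevertheless names motivation as what the comparison can settle. If the sentence is followed, a difference between self-selected groups may be read as evidence about motivation, and the absence of a difference as evidence against it. Neither reading is warranted. At stake is the interpretation of one of the two stated reasons for the preference design, namely relating preference to outcome.

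**Working it through.** **Step 1: how the groups arise.** Recruitment of practices and patients makes group membership depend on the patient's stated preference. Randomisation and blinding applies only to those without one. The preference-versus-randomised contrast is therefore observational, as the protocol's own label for that arm acknowledges.

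**Step 2: is motivation measured?** The Outcomes, Medical records and Questionnaires sections list biomarkers, blood pressure, Body Mass Index, smoking, physical activity, work loss, health status, diabetes distress, treatment satisfaction and medication adherence. None is a measure of motivation. Being in a preference group has to stand in for it.

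**Step 3: is preference a fair stand-in?** A strong wish for three-monthly control might reflect commitment, anxiety or habit. A strong wish for six-monthly control might simply mean wanting fewer visits. The sentence would treat both groups as more motivated. Patients without a strong view on frequency are not thereby less motivated.

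**Step 4: is the comparison tied to the expected differences?** The plan will look for determinants of preference. Any of these that also predicts control is a confounder of the outcome comparison. The section does not say that they enter that comparison. ANCOVA is named for other data: "Data from the questionnaires at the start and at the end of the intervention period will be analysed using ANCOVA".

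**Step 5: the plan's figure.** The point challenges no figure, but the sample size is used in Step 6. With p = 95, δ = 5 and Z values 1.96 and 1.28 from the Sample size calculation section:

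n = 2 × 95 × 5 × (1.96 + 1.28)² / 5² = 950 × 10.4976 / 25 = 398.9, rounded up to 399 per randomised group, as stated.

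**Step 6: illustration, with assumed values that are not in the document.** Suppose motivation and preference have no effect. One yes/no patient characteristic raises the probability of good control from *l* to *h*, and a share *a* of the preference group and *b* of the randomised group have it. The difference from confounding alone is (a − b)(h − l).

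- Smallest case: h = 97%, l = 91%, a = 60%, b = 50%. Difference 0.10 × 6 = 0.6 points (94.6% against 94.0%).
- Largest case: h = 97%, l = 88%, a = 80%, b = 40%. Difference 0.40 × 9 = 3.6 points (95.2% against 91.6%).

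Take 399 per group. For a preference group this is a further assumption: the protocol gives only 798 for the two observational arms together, and 798 / 2 = 399. The probability that an unadjusted two-sided 5% test favours the preference group is Φ((d − 1.96·SE₀)/SE₁), with d the difference, SE₀ the pooled and SE₁ the unpooled standard error.

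- Smallest case: (0.006 − 1.96 × 0.01641) / 0.01641 = −1.59, giving about 5.5%.
- Largest case: (0.036 − 1.96 × 0.01758) / 0.01753 = 0.09, giving about 53.5%.

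Without confounding this probability would be 2.5%. The direction was chosen for the illustration; the imbalance could equally run the other way.

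**The case against.** Four stronger readings are tempting, and the document does not support them.

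- *The plan claims that motivation improves control.* It does not. The wording is conditional, and nowhere does the plan commit to reporting a causal effect. The Study design section speaks of a relationship with preference, which is close to the restatement proposed here.
- *The comparison will be crude.* The article never says so. It is a condensed account, and the covariates for a secondary comparison are commonly left to a fuller document. The search for determinants of preference is also placed within these same analyses. All that can be said is that no adjustment is stated.
- *The applicability of the results falls with the motivation claim.* In the Analysis section, applicability follows from the determinants and risk profiles. It would stand if the motivation clause were removed.
- *The bias can be judged against the ±5-point margin, or threatens the trial's conclusion.* That margin belongs to the equivalence comparison of the randomised groups, which does not use the preference groups.

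It is also fair to say that all participants are selected on the same limits for HbA1c, systolic pressure and cholesterol. This narrows the room for imbalance but does not exclude it.

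These replies limit the point without removing it. An unseen covariate model could reduce confounding by measured characteristics, but it could not turn a preference for a visit frequency into a measure of motivation. That inference is stated in the text and is not a matter of omitted detail.

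**Conclusion.** The point holds as a modest finding about secondary comparisons. The stated inference about motivation does not follow from a contrast of self-selected groups in which motivation is unmeasured. The missing link between the determinants of preference and the outcome comparison is a weaker, supporting observation.

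The real bias, in size or direction, cannot be obtained from the document. The range of 0.6 to 3.6 points, with a false finding in favour of the preference group in about 5.5% to 53.5% of trials, rests wholly on the assumed prevalences, control rates and group size. It shows only that selection can produce an apparent result. The primary equivalence comparison is unaffected.

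**What to change.** Replace the motivation clause in the Analysis section with a statement that the association between having a strong preference and cardiometabolic control will be explored, separately for each visit frequency, without attributing it to motivation.

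State that this association is estimated in a model adjusted for pre-study HbA1c, systolic pressure, total cholesterol and medication (Medical records section) and for age, sex and education (Questionnaires section). Whether to add a practice effect can be left to the analysis plan. Report the result as exploratory, with a confidence interval and a note that unmeasured differences may remain.

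The cost is one reworded sentence and one adjusted model for each comparison. No new data, patients or visits are needed.

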**Figure 2 F2:**
[figure not shown]
**Group comparisons**. An overview of all comparisons that will be made between the four groups. The solid arrow is the comparison to answer the main research question. The dotted arrows are other comparisons that will be made.

#### Economic evaluation

Should this study demonstrate equivalent outcomes with different frequencies of diabetes monitoring, the evident cost-reduction of less control visits merit the conclusion that six-monthly monitoring is the approach of first choice and a cost-minimisation analysis will be done. This is likely to provide sufficient evidence to change the frequency of monitoring in well-controlled type 2 diabetes patients in general practice.

However, should the three-monthly follow-up scheme result in a better cardiometabolic control, a cost-effectiveness analysis will be performed. If better outcomes can be realised with a higher control frequency at an associated higher cost to society, or vice versa, (somewhat) worse patient outcomes at a lower cost, the balance between costs and outcomes is of interest. Differences in the number of QALYs between groups during the study period will be assessed. The difference in treatment effect will be calculated as follows: for each group the difference between baseline and final measurements in percentage of patients with good cardiometabolic control will be determined. The absolute difference between measurements pre- and post-intervention will be taken as the intervention effect. Accordingly, differences in QALYs between groups will be calculated. The 'incremental cost-effectiveness ratio' (ICER) will be expressed as cost differences between groups divided by differences in treatment effects between groups. Confidence intervals will be determined using bootstrapping [19]. A 'cost-effectiveness acceptability curve' (CEAC) will also be drawn using the bootstrap sample. Cost-utility estimates will be derived accordingly, using QALY differences between groups as outcome measure.

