**Methods and design:**

The study is a randomised controlled patient-preference equivalence trial. Participants are asked if they prefer three-monthly (usual care) or six-monthly diabetes monitoring. If they do not have a preference, they are randomised to a three-monthly or six-monthly monitoring group. Patients are eligible for the study if they are between 40 and 80 years old, diagnosed with type 2 diabetes more than one year ago, treated by a general practitioner, not on insulin treatment, and with HbA1c ≤7.5%, systolic blood pressure ≤145 mmHg and total cholesterol ≤5.2 mmol/l. The intervention group (six-monthly monitoring) will receive the same treatment with the same treatment targets as the control group (three-monthly monitoring). The intervention period will last one and a half year. After the intervention, the three-monthly and six-monthly monitoring groups are compared on equivalence of cardiometabolic control. Secondary outcome measures are HbA1c, blood pressure, cholesterol level, Body Mass Index, smoking behaviour, physical activity, loss of work due to illness, health status, diabetes-specific distress, satisfaction with treatment and adherence to medications. We will use intention-to-treat analysis with repeated measures. For outcomes that have only baseline and final measurements, we will use ANCOVA. Depending on the results, a cost-minimisation analysis or an incremental cost-effectiveness analysis will be done.

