#### Questionnaires

The participants will be asked to complete an extensive questionnaire before (t = 0) and after (t = 18 months) the intervention period. This questionnaire comprises general background information on age, gender, ethnicity, education, smoking, physical activity, occupation and loss of work due to illness, health status, diabetes-specific distress and satisfaction with diabetes treatment.

Current smoking is measured as the number of cigarettes per day or the number of cigars per week. Smoking in the past is measured the same way. Also the number of pack years is recorded. Physical activity is measured with the Short Questionnaire to Assess Health-enhancing physical activity (SQUASH) [10]. The SQUASH is a reliable and valid questionnaire to measure the level of physical activity in an adult population. The questionnaire was designed to give an indication of the habitual activity level. Information on light (range: 2-4 Metabolic Equivalent of Task (MET)), moderate (range: 4-6.5 MET) and vigorous (>6.5 MET) intensity physical activities will be obtained. Physical activity will be expressed in minutes per week and in a total activity score. The total activity score will be calculated by multiplying the minutes per week by the actual MET score of the specific activity (MET/min/week).

Occupation and loss of work due to illness are measured with the Short Form Health and Labour Questionnaire (SF-HLQ) [11]. The SF-HLQ consists of three parts: absenteeism from paid work, production losses without absenteeism from paid work and hindrance in the performance of paid and unpaid work. Data derived with this questionnaire will be used to calculate costs of productivity losses, should incremental cost-effectiveness be merited at closure of the trial (see **economic evaluation**).

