#### Economic evaluation

To be able to calculate direct health care costs, data on health care use are needed. Data concerning consultations beyond the planned monitoring consultations, medication use and referral rates to other health care professionals will be collected from the general practitioners' computerised Information System. Should this trial provide evidence that three-monthly monitoring results in better outcomes than six-monthly monitoring, an incremental cost-effectiveness analysis becomes warranted, that quantifies the additional cost related to the additional health effects. For such an economic evaluation we will use data on health care use as recorded in the information system of the general practitioners, and data recorded with the SF-HLQ and the EQ5D (see above). The EQ5D is of special importance, as utilities, and consequently, quality adjusted life years (QALYs) can be elicited using this generic questionnaire.

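### The economic analysis is chosen by the clinical result, has no stated branch for an inconclusive or six-monthly-better trial, and under equivalence fixes its conclusion before costs and QALYs are compared

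*Protocol article*

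**What the plan says.** The Abstract (Methods and design) announces a choice between two methods: "Depending on the results, a cost-minimisation analysis or an incremental cost-effectiveness analysis will be done".

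The Economic evaluation part of the Analysis section gives the triggers.

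- **Equivalence shown.** "Should this study demonstrate equivalent outcomes with different frequencies of diabetes monitoring, the evident cost-reduction of less control visits merit the conclusion". The conclusion meant is a preference for the six-monthly schedule, and a cost-minimisation analysis is done.
- **Three-monthly better.** "However, should the three-monthly follow-up scheme result in a better cardiometabolic control, a cost-effectiveness analysis will be performed". The incremental cost-effectiveness ratio, the acceptability curve, the cost-utility estimates and the statement "Confidence intervals will be determined using bootstrapping" all appear after this sentence.

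The Economic evaluation part of the Outcomes section repeats the second trigger in firmer terms: "Should this trial provide evidence that three-monthly monitoring results in better outcomes than six-monthly monitoring, an incremental cost-effectiveness analysis becomes warranted". The Questionnaires section ties productivity costs to the same branch; they are to be calculated "should incremental cost-effectiveness be merited at closure of the trial".

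The Discussion recommends the lower frequency if cost-effectiveness is proven.

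**The concern.** There are two problems, and both lie in the rule that the article itself states.

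First, the two triggers do not cover all results. An equivalence trial can end with an interval that crosses a margin and also includes zero, so that neither equivalence nor a difference is shown. It can also end with six-monthly monitoring shown better. Neither result has a stated economic analysis. The trial's stated aim is efficiency, so an inconclusive clinical result is one where a joint estimate of costs and health effects would be especially useful.

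Second, in the equivalence branch the economic conclusion is fixed in advance. Equivalence within 5 points on a yes/no composite of HbA1c, systolic blood pressure and total cholesterol shows neither equal QALYs nor lower total cost. Yet the methods that would carry the uncertainty in cost and effect together are described only in the other branch. The Discussion makes its recommendation depend on proven cost-effectiveness, but no cost-effectiveness analysis is planned in the branch that would lead to that recommendation.

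**Working it through.** **Inputs (Sample size calculation section):** 399 per randomised group; expected success 95%; equivalence if the two-sided 95% interval lies wholly within −5 to +5 points; z = 1.96 and 1.28. The true differences other than zero used below are assumptions.

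**Step 1. Reproduce the plan's figure.** n = 2p(100 − p)(1.96 + 1.28)² / δ² = 2 × 95 × 5 × 3.24² / 25 = 398.9, so 399. This agrees.

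**Step 2. Interval width at 95% success in both groups.**
- SE = √(2 × 0.95 × 0.05 / 399) = 0.0154, or 1.54 points.
- Half-width = 1.96 × 1.54 = 3.02 points.

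**Step 3. Split the results when there is no true difference.**
- Equivalence requires an observed difference within ±(5 − 3.02) = ±1.98 points. 1.98 / 1.54 = 1.28, and 2Φ(1.28) − 1 = 0.80.
- Three-monthly shown better (interval wholly above zero): 0.025.
- Six-monthly shown better: 0.025.
- Inconclusive: 1 − 0.80 − 0.025 − 0.025 = 0.15.

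These categories do not overlap, because the half-width exceeds 2.5 points and an interval cannot both exclude zero and stay inside the margin. Results with no stated branch total 15% + 2.5% = 17.5%.

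The 80% is below the stated 90% power because equivalence requires both limits to be met and the formula uses 1.28 for a single limit. That is a separate matter. Taking 90% at face value, 1 − 0.90 − 0.025 = 7.5% still have no branch.

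**Step 4. Allow a true deficit for six-monthly monitoring.** Example for 2 points (95% against 93%):
- SE = √((0.95 × 0.05 + 0.93 × 0.07) / 399) = 1.68 points; half-width 3.29.
- Equivalent: observed difference within ±1.71, probability 0.42.
- Three-monthly better: 1 − Φ((3.29 − 2) / 1.68) = 0.22.
- Six-monthly better: below 0.001.
- Inconclusive: 0.36.

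| True deficit (points) | Equivalent | Three-monthly better | Six-monthly better | Inconclusive |
|---|---|---|---|---|
| 0 | 80% | 2.5% | 2.5% | 15% |
| 2 | 42% | 22% | <0.1% | 36% |
| 3 | 20% | 41% | ~0% | 39% |
| 5 | 2.5% | 77% | ~0% | 21% |

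A simulation of 400,000 trials per row gives inconclusive shares of 16%, 36%, 38% and 20%.

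**Step 5. Sensitivity to the number analysed.** Half of the 1800 to be recruited are expected to be randomised, which is 450 per group. If all counted in full (an assumption that favours the plan), the inconclusive share is 9% at no difference and 29% at 2 points.

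**Step 6. What the equivalence branch leaves out.** This needs no arithmetic. Cost-minimisation compares costs alone. The QALY difference, its correlation with cost, the acceptability curve and productivity costs belong to the other branch in the text as written.

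**The case against.** The strongest defence is that the Abstract promises one of the two analyses in any event. The rule could then be read as a simple split: equivalence leads to cost-minimisation, anything else to cost-effectiveness. The Analysis section also says that somewhat worse outcomes at lower cost make the balance of interest, and sets no significance criterion there. This has some force, but it does not close the gap. The Outcomes section asks for evidence that three-monthly monitoring is better. If better meant only a better point estimate, inconclusive trials with an estimate favouring six-monthly would still have no stated analysis. The remark on worse outcomes at lower cost describes the same trade-off from the other side and adds no branch.

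Cost-minimisation after pre-specified equivalence is also a recognised choice made before the data are seen. That is fair. The objection is to the conclusion fixed in advance and to leaving joint uncertainty out of it.

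A reader might go further in four ways that the document does not support.

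- **That offsetting costs are ignored.** The Outcomes section collects "Data concerning consultations beyond the planned monitoring consultations, medication use and referral rates" without condition, so cost-minimisation can include them. The remark on an evident saving refers to control visits.
- **That health status is not examined under equivalence.** Health status is a secondary outcome and questionnaire data go to ANCOVA whatever the primary result. What is conditional is combining health effects with costs.
- **That QALYs are miscalculated as a pre/post change.** The sentence "Accordingly, differences in QALYs between groups will be calculated" follows a pre/post definition, but that definition is for the percentage under good control. The same paragraph speaks of QALYs over the study period, which allows an area under the utility curve. No error is fixed here.
- **That most trials would have no branch, because success may fall well below 95%.** The document assumes 95% and gives no other rate. A lower rate is a sample-size question and is not used here.

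**Conclusion.** The point stands. As written, the economic method depends on the clinical result, an inconclusive or six-monthly-better trial has no stated analysis, and the equivalence branch reaches its conclusion before total costs are compared and without joint uncertainty in cost and QALYs.

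Under the plan's own inputs and no true difference, about 15% of trials are inconclusive and a further 2.5% show six-monthly better. At an assumed 2-point deficit about 36% are inconclusive. At 5 points three-monthly better dominates and the gap is smaller, so it would be wrong to say that a failed equivalence claim usually has no analysis. These figures rest on 95% success with three-monthly monitoring, 399 analysed per group and a normal approximation.

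The primary clinical comparison is unaffected. The article condenses a fuller protocol, but this is not a missing detail: several sections state the conditional rule, and that rule is what needs changing.

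**What to change.** In the Economic evaluation part of the Analysis section, with matching wording in the Abstract, the Questionnaires section and the Economic evaluation part of the Outcomes section:

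1. Run the bootstrapped analysis already described, of incremental costs and incremental QALYs jointly with the acceptability curve, for the randomised comparison whatever the primary result.
2. Include productivity costs unconditionally, alongside consultations, medication and referrals.
3. State that QALYs are those accrued over the 18 months, with the difference adjusted for baseline utility.
4. Keep cost-minimisation as a secondary view when equivalence is shown.
5. Replace the automatic preference under equivalence with a conclusion based on the estimated incremental costs and QALYs and their uncertainty. This also brings the section into line with the Discussion's condition of proven cost-effectiveness.

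The sample size does not change and no new data are needed: EQ-5D and SF-HLQ are collected at 0 and 18 months, and resource use comes from practice records. The price is modest extra analysis and, under equivalence, a conclusion that carries more stated uncertainty.
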